### Randomisation

The unit of randomisation for this trial is the RACF (not the resident). Once the 18 RACFs selected for the stepped-wedge trial have provided consent to participate, each RACF will be randomised to a transition date by a statistician (Fig. 3). RACFs will be advised of their scheduled start date for crossover to the AMS ENGAGEMENT bundle 3 months in advance. This allows time to make the necessary arrangements for the intervention (convene AMS team for the facility, undertake an AMS needs assessment using the NAT, select and localise elements of the AMS ENGAGEMENT bundle). Each facility will spend 1-month in transition before sequentially crossing over to the implementation phase. The maximum time a facility can be in the implementation will be 18 months and the minimum will be 1 month (Fig. 3).

### Allocation concealment and blinding

The randomisation schedule will be accessible only by the statistician. Once a RACF has been informed of their start date, blinding of the intervention to RACF staff and GPs servicing the facilities is not possible as the educational elements of the AMS ENGAGEMENT bundle directly targets this group of clinicians. The research team members working with RACFs during the observation period will also not find out a facility’s randomisation until 3 months prior to their crossover date. A statistician not involved in the day-to-day management of the trial will generate and maintain the random allocation sequence for RACFs to transition from control to intervention.

### Data collection, management and monitoring

De-identified data will be provided by participating RACFs. Based on data sourced from pharmacy dispensing reports, infection control registers and electronic records systems, RACFs will provide monthly reports on antibiotic dispensing (as a proxy measure for consumption); suspected infections; number and types of pathology tests conducted relating to suspected UTIs or *C. difficile* infections; and details of resident hospitalisations, including admission and discharge dates, reason for hospitalisation and any additional medications or diagnoses related to the hospitalisation. Baseline data will be collected on residents’ demographics, co-morbidities (supplied annually to the Commonwealth Department of Health (i.e. the Aged Care Funding Instrument)), number of regular medications and current antibiotics. Antibiotics include all systemic antibacterials (the Anatomical Therapeutic Chemical (ATC) level J01) and topical antimicrobial agents.

An appropriately trained and authorised delegate at each facility will undertake data collection and reporting. This delegate will de-identify resident data prior to uploading to The University of Queensland’s secure Research Data Management platform, where it will be transferred into a REDCap© database. Only authorised users at each facility will be able to upload data using a unique username and password. The trial database will be stored securely on The University of Queensland network. A central coordinating centre (the Australasian Kidney Trials Network in the Centre for Health Services Research at The University of Queensland) will perform research data management and data cleaning. Access to research data will only be granted to staff involved in the cleaning and analysis of research data. The central coordinating centre will conduct on-site and remote monitoring at each RACF, on a quarterly basis or more frequently if needed, to ensure the accuracy and consistency of data collection and data management. This will include the comparison of source and trial data. The study design is open label so unblinding will not occur.

### Economic evaluation

The primary economic analysis will be a cost analysis of the intervention period compared to the control period. The following costs will be factored into the cost analysis:Pathology and medication costs of RACF residentsAvailable information on resident hospitalisations, including treatments administeredCost of providing nurse and general practitioner educationCost of telehealth service provisionStaff time spent on other AMS activities, i.e. AMS team meetings and resident education.

Costs will be assigned to resource usage using Medicare Benefits Scheme and Pharmaceutical Benefits Scheme item numbers and cost weights for hospitalisations. A generalised linear mixed model using appropriate family and link for the underlying distribution will be used to compare groups and account for the clustering effect of the RACF.

To ascertain the impact of reduced antibiotic usage in RACFs, a cost-effectiveness model will be developed from the health service payer perspective. The surrogate outcome of reduced usage will be transformed to a final outcome of reduction in AMR infections in residents in order to assess the longer-term costs and outcomes over the lifetime of residents. The model will incorporate subsequent changes in second-line treatments, longer treatments and more diagnostics. This will be based on trial data supplemented with literature estimates and/or expert opinion where data is not available. Utility will be assigned according to population values for this cohort with decrements applied for adverse outcomes.

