#### Randomisation of RACFs

The 18 RACFs will be randomly assigned to an intervention starting time in a stepped-wedge RCT. The trial will be conducted across a 20-month observation period. The first month will be a control period for all sites; one site will transition from control to intervention each month for 18 months based on their randomisation; the final month will be an intervention period for all sites.

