### Sample size

Sample size was calculated based on the outcome of antibiotic consumption as measured by DDDs. For a trial to run over 20 months with a mean cluster size of 50 residents and a control event rate of 120 DDDs per 1000 resident days [22, 42], 18 RACFs will provide 82% power to detect a 20% reduction in DDDs, which has been demonstrated as feasible by other studies [28, 43] (although these studies have utilised other metrics to quantify antibiotic consumption). The power calculation is based on a conservative intra class correlation coefficient (ICC) of 0.012 and coefficient of variation of 0.3 [44].

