### Statistical analysis

The primary outcome is DDDs of antibiotics per 1000 occupied bed days. DDDs will be measured at the patient level monthly and analysed using a generalised linear mixed model for count data. The model will include fixed effects for intervention (AMS ENGAGEMENT vs control) and calendar time (randomised crossover times) and two random effects, one for variation among RACFs and a second to accommodate repeated measures over time on participants. Analysis will be by the intention-to-treat-schedule; that is, calendar time in the statistical model will be the randomised crossover times irrespective of whether crossover actually occurred at the pre-specified time. If there are discrepancies between randomised and actual crossover times, a supporting analysis will use the actual time that crossover occurred. Results will be expressed as rates per 1000 occupied bed days with 95% confidence intervals.

Data from the transition months will be reported but not included in the final analysis. All data will be analysed using SAS software (SAS Institute Inc., Cary, NC, USA). For the primary analysis, a *P* value less than 0.05 will be considered statistically significant. A statistical analysis plan will describe in detail the pre-specified analysis for all efficacy and safety outcomes and be available in the public domain before database lock.

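### The cost model is described as a comparison of periods with facility clustering and no calendar-time term, so in this stepped wedge a common trend would bias the cost difference

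*Protocol article*

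**What the plan says.** The Economic evaluation section sets the contrast: "The primary economic analysis will be a cost analysis of the intervention period compared to the control period". It then gives the model: a generalised linear mixed model, with family and link still to be chosen, that "will be used to compare groups and account for the clustering effect of the RACF". The terms named are group and facility. Pathology, medication and hospitalisation costs are among the inputs, alongside the costs of delivering the bundle.

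The Statistical analysis section treats the primary outcome differently. That model has fixed effects for intervention and for calendar time, plus random effects for facility and for participant, and leaves transition months out. The same section promises a statistical analysis plan for efficacy and safety outcomes. It does not mention costs, and the Economic evaluation section does not refer back to the primary model.

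Net cost is a listed secondary outcome, and cost-effectiveness is one of the three aims.

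**The concern.** In a stepped wedge, the intervention phase comes later than the control phase by construction. Anything that changes over the calendar in all facilities is therefore partly carried by the treatment contrast unless time is in the model. Accounting for clustering by facility does not help: it moves weight towards the before-and-after comparison within each facility, where the time gap is largest.

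The protocol makes a trend plausible. The Background cites a ten-year rise in antibiotic use in Australian facilities, and the section on site retention places the trial in the COVID-19 pandemic. If admissions, pathology or medication use rises over the trial for unrelated reasons, the bundle looks more costly than it is. If they fall, it looks cheaper.

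**Working it through.** **Schedule.** From the section Randomisation of RACFs: "The trial will be conducted across a 20-month observation period"; "The first month will be a control period for all sites"; one site then moves each month for 18 months, and all sites are in intervention in the last month. Number the sites k = 1 to 18 in crossover order. Site k is in control in months 1 to k, in transition in month k+1, and in intervention in months k+2 to 20.

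**The plan's own figure.** The sample size section states that "18 RACFs will provide 82% power to detect a 20% reduction in DDDs", from a "mean cluster size of 50 residents and a control event rate of 120 DDDs per 1000 resident days" and a "conservative intra class correlation coefficient (ICC) of 0.012 and coefficient of variation of 0.3". I used the Hussey-Hughes variance with 18 sequences of one facility, 50 residents per facility-month, transition month excluded, ICC 0.012, two-sided alpha 0.05 (sidedness is not stated) and 20 month effects. The outcome was treated as a proportion with pooled variance 0.108 × 0.892, and the difference is 0.120 − 0.096 = 0.024.

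- With month effects: SE 0.00837; 0.024/0.00837 − 1.96 = 0.91; power 81.8%.
- Without month effects: SE 0.00554; 0.024/0.00554 − 1.96 = 2.37; power 99.1%.

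The stated 82% agrees with a time-adjusted analysis. This does not test the cost model, but it shows that the design was sized with time in mind.

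**Separation in time, transition months excluded.**

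- Control site-months: Σk = 171. Intervention site-months: Σ(19 − k) = 171.
- Mean control month: Σ k(k+1)/2 ÷ 171 = 1140/171 = 6.67.
- Mean intervention month, by symmetry: 21 − 6.67 = 14.33. Pooled gap: 7.67 months.
- Within site k: (k+22)/2 − (k+1)/2 = 10.5 months, the same for every site.
- If the transition month were counted as intervention, the within-site gap would be (k+21)/2 − (k+1)/2 = 10 months.

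**Bias from a common linear trend, as a multiple of the monthly slope.**

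| Model | Bias |
|---|---|
| No facility effect, no time | 7.7 |
| Random facility intercept (ICC 0.012, 50 residents), no time | 10.2 |
| Fixed facility effects, no time | 10.5 |
| Random facility intercept, month effects | 0 |

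No ICC for cost is given. The multiplier for a cost model without time therefore lies between 7.7 and 10.5, depending on how strongly costs cluster.

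**Size under assumed drifts.** The documents state no drift, so these rates are assumptions. For a proportional drift d per year, the spurious ratio is (1+d)^(10.19/12).

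- 3% per year: 1.03^0.849 − 1 = 2.5%.
- 5% per year: 1.05^0.849 − 1 = 4.2%.
- 10% per year: 1.10^0.849 − 1 = 8.4%.
- A 10% fall per year: 0.90^0.849 − 1 = −8.6%.

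At 10% per year, the multipliers 7.67 and 10.5 give 6.3% and 8.7%.

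**Price of adjustment.** On the consumption inputs, month effects multiply the variance by (0.00837/0.00554)² = 2.28. The protocol gives no standard deviation for cost, so this is an illustration only.

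**The case against.** The best defence is that the cost sentence states what the model is for and is not a list of its terms. It leaves even the distribution open, it nowhere says that time is excluded, and a fuller economic plan could add it. That stands as far as it goes: this is an omission in the wording. But the article does name the contrast and the adjustment, it names calendar time where the primary model has it, and its deferral to an analysis plan does not mention costs. An analyst following the text would fit a model without time.

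The effect on the economic conclusions is also limited in two ways. Education, telehealth and stewardship staff time are largely costs of delivering the bundle and would not follow a trend in admissions. And the cost-effectiveness model starts from the reduction in antibiotic use, whose analysis does adjust for time. Both points stand. The bias concerns the pathology, medication and hospitalisation components of net cost.

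A reader might infer more from the list of secondary outcomes.

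- **Harm models.** Mortality, admissions and *C. difficile* cases are listed as contrasts between the phases, which could suggest that their analyses also omit time. The list defines outcomes and gives no model, and the safety analyses are left to a plan that is not shown. The primary contrast is also worded as bundle versus control and is still adjusted for time. At most, the median rates across facilities should be labelled descriptive, because a crude median carries no time adjustment.
- **Year-on-year mortality.** Each site has only k + (19 − k) = 19 months outside transition, so none has 12 in each phase. It does not follow that the measure cannot be formed. Site k has control month m and intervention month m+12 for every m from max(1, k−10) to min(8, k). Every site has at least one such pair: months 1 and 13 for k = 1, and months 8 and 20 for k = 18.

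Nor does the protocol say that unit prices will vary over the trial; it only leaves the price year unstated.

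**Conclusion.** The point holds for the cost model. As described, it compares phases that are 10.5 months apart within every facility and has no term for calendar time. A trend common to all facilities would bias the difference by about 10 times its monthly size (7.7 to 10.5, depending on the clustering of costs). The time separation follows from the published schedule alone. The size in per cent is conditional: about 2.5% to 8.4% for assumed drifts of 3% to 10% per year, applied to the cost components that drift. With no trend there is no bias. The documents do not show that the harm analyses omit time, and they do not rule out a year-on-year mortality comparison within a facility. This is a clarification that should be made before the cost data are analysed; it does not affect the primary outcome.

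**What to change.** In the Economic evaluation section or a separate economic analysis plan, state that:

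1. the cost model includes fixed effects for calendar month, or a smooth function of time, as the primary model includes calendar time;
2. transition months are handled by a stated rule. Induction education is delivered in that month, so simply dropping it would also drop part of the cost of the bundle; one option is to leave those months out of the comparison and add set-up costs separately;
3. resource use is valued at one constant price year.

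In the list of secondary outcomes, label the median rates across facilities as descriptive.

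The cost is a few sentences and one factor in a model already planned. Intervals will be wider, with about 2.28 times the variance on the consumption inputs, but the narrower interval is not valid if a trend exists. If 20 month effects prove unstable for skewed cost data, a smooth time term is the fallback, and it should be named in advance.

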### Process evaluation of AMS ENGAGEMENT

A comprehensive process evaluation will be conducted to identify the primary needs of RACFs with respect to AMS and to explore the barriers and enablers of stewardship programme. A mixed-methods evaluation to understand the functioning of the AMS ENGAGEMENT interventions will use data collected during the stepped-wedge trial and qualitative data collected during and after the trial. The evaluation will examine implementation, mechanisms of impact and contextual factors using a RE-AIM framework (reach, effectiveness, adoption, implementation, maintenance) [45] (Supplementary Material).

Qualitative data collected specifically for the process evaluation will include transcripts of the first AMS meeting at each RACF, pre- and post-intervention staff surveys and post-completion interviews with AMS team members. The first AMS meeting will be a facilitated workshop with members of the AMS team to review the facility’s Needs Assessment. Meeting transcripts will be analysed using inductive thematic analysis to identify contextual factors at each facility, as well as barriers and enablers to AMS implementation. RACF staff will be invited to participate in a pre-implementation survey 3 months prior to their facility’s implementation date and within 3 months of trial completion. The surveys will elicit perspectives on organisational readiness, staff beliefs about antibiotic use and barriers to change, and the Conditions for Work Effectiveness Questionnaire II (CWEQII) [46] will be administered to measure change in structural empowerment of nursing staff. Semi-structured interviews will be conducted within 3 months of trial completion with a purposively selected sample of AMS team members to review barriers and enablers and to assess intervention maintenance. Individual consent will be provided by all workshop, survey and interview participants prior to their participation in qualitative data collection. Participant confidentiality will be protected through the use of pseudonyms for workshop and interview transcripts, and by not tracking individual survey responses.

### Challenges: retention of sites

Recruitment and retention of RACFs will be challenging in the midst of the COVID-19 pandemic. The following strategies will be adopted to optimise recruitment and retention:All components of the AMS ENGAGEMENT bundle will be designed for remote delivery through mediums such as print materials, videoconferencing, teleconferencing, webinars and online tutorials and videos (to mitigate the risk of COVID-related restrictions limiting participation).A representative from a RACF will be included on the Trial Steering Committee to ensure the protocol and interventions are designed and implemented with feasibility in mind.The research management team will be accessible to participating facilities during the planning and needs assessment to address questions and respond to any concerns.All interventions, including AMS team meetings, will be scheduled to suit the operational and care delivery needs of participating facilities.A dedicated member of the research team will maintain regular (at least monthly) contact with a liaison from each facility prior to and during the observation period to proactively identify and address any obstacles to participation.

The risk remains that facilities will discontinue their participation during the observation period for a number of reasons, including resourcing limitations, preference for early intervention of the AMS ENGAGEMENT bundle, COVID-19 impacts or changes in organisation or facility management. Additionally, aged care service providers with multiple RACFs enrolled in the trial may not want to wait to implement an AMS programme across all facilities if is it well received and/or proving effective. This risk may be mitigated by making the publicly accessible components of the AMS ENGAGEMENT bundle (e.g. guidelines) available to these facilities, but discouraging the sharing of facilitated interventions such as the education materials, telehealth webinars and nursing telephone support. The research team will also specifically request information on any AMS activities conducted at the facility at their regular monthly contact.

### Trial safety monitoring

Trial safety will be monitored by an internal safety reviewer, who will be an infectious disease expert associated with the trial (but not a member of the TSC). This decision is based on findings of a recent trial of an AMS programme in 12 US RACFs [18] and a systematic review which included studies that evaluated the impact of AMS on health outcomes and health care utilisation [34]. Both studies found no significant differences in all cause hospital admissions or mortality between RACFs who received AMS-related interventions and those that did not. The appointment of an internal safety reviewer is also consistent with the Australian *National Statement on Ethical Conduct in Human Research (2007)* (National Statement) which “permits monitoring arrangements to be commensurate to the risk, size and complexity of the trial. The nature and extent of participant safety monitoring should be based on the assessment of the risks of the trial intervention(s) relative to standard care and the extent of knowledge about the IMPs/IMDs being tested. The sponsor’s plans for safety monitoring should be documented and continually reviewed and adapted during the trial, as real time assessments of safety data are performed.”

The Central Coordinating Centre (UQ) will prepare reports for the safety reviewer on resident hospitalisation, infection and mortality rates based on RACF monthly data submissions. Reports will be supplied to the safety reviewer, who will request further information, where applicable, on any significant deviations (≥1SD) from the trend.

### Dissemination of findings

Dissemination of trial results will occur in accordance with the Trial Management Plan. Dissemination activities will include:Post-implementation workshops with participating RACFs and their governing bodies (where applicable)Academic papers, presentation at scientific conferencesFinal report with key findings and recommendations for a broader rollout of AMS activities in Australian RACFs.

No participating RACFs, their staff or residents will be identified during research dissemination activities.

### Protocol modifications

Any modifications to the protocol which may impact on the conduct of the trial, have potential benefit to the participant/s or may affect participant safety, including changes of trial objectives, trial design, trial population, sample size, trial procedures or significant administrative aspects, may require a formal amendment to the protocol. Such amendment will be agreed upon by the Trial Steering Committee and approved by the relevant ethics committee prior to implementation and will be communicated in writing and at quarterly meetings.

### Authorship policy

To qualify for authorship, a contributor should:Have made substantial contributions to the conception or design of the work; or the acquisition, analysis, or interpretation of data for the work; or the creation of new software used in the work; or have drafted the work and substantially revised itHave approved the submitted version (and any substantially modified version that involves the author’s contribution to the trial); ANDHave agreed both to be personally accountable for the author’s own contributions and to ensure that questions related to the accuracy or integrity of any part of the work, even ones in which the author was not personally involved, are appropriately investigated, resolved, and the resolution documented in the literature.

All contributors who meet the first criterion will be given the opportunity to qualify for authorship.

